## Abstract

**Background:**

Laparoscopy-assisted vaginal hysterectomy is one of the definite methods for the treatment of symptomatic uterine fibroids with lesser intraoperative bleeding and shorter hospitalization compared with abdominal hysterectomy. However, laparoscopy-assisted vaginal hysterectomy cannot preserve uterus and can show postoperative complications by the change of pelvic structure. Thus, laparoscopic uterine artery ligation has been introduced for relieving the symptoms caused by uterine fibroids in place of hysterectomy. The current study was designed to compare postoperative quality of life between laparoscopic uterine artery ligation and laparoscopy-assisted vaginal hysterectomy, and to evaluate the efficacy of laparoscopic uterine artery ligation which can treat symptomatic uterine fibroids with the preservation of uterus.

**Methods and design:**

Patients enrolled the current study are randomized to laparoscopic uterine artery ligation or laparoscopy-assisted vaginal hysterectomy. The primary outcome is to compare postoperative quality of life between laparoscopic uterine artery ligation and laparoscopy-assisted vaginal hysterectomy using the European Organization for Research and Treatment of Cancer Quality of Life Questionnaire for Cancer patients version 3.0. Secondary outcomes are to evaluate the volume reduction of uterus, uterine fibroids and ovaries by the 2 treatments, to compare the improvement of subjective symptoms using 11-point symptom score and postoperative clinical outcomes between laparoscopic uterine artery ligation and laparoscopy-assisted vaginal hysterectomy, and to investigate the improvement of postoperative vaginal bleeding by laparoscopic uterine artery ligation.

**Discussion:**

Among treatment methods for symptomatic uterine fibroids with the preservation of uterus, laparoscopic uterine artery ligation is expected to have the efficacy like uterine artery embolization, which appeared to be safe for routine use with symptomatic relief. The current study fully recruited in June 2008 and the results will be available in June 2009. If there is no difference of postoperative QOL between laparoscopic uterine artery ligation and laparoscopy-assisted vaginal hysterectomy for the treatment of symptomatic uterine fibroids, the comparison of quality of life between laparoscopic uterine artery ligation and uterine artery embolization will be also needed as a surgical treatment for preserving uterus.

**Trial registration:**

Current Controlled Trials ISRCTN76790866

## Background

Uterine fibroids are the most common benign uterine tumors. They may be more common in women who are obese, and there appears to be an increased familial incidence [1]. Although fewer than one half of them are estimated to produce symptoms [2], uterine fibroids may cause different symptoms including menorrhagia, intermittent menstrual bleeding, pelvic pain, urinary frequency and constipation.

The management of uterine fibroids is dependent on the patient's age and proximity to anticipated menopause, symptoms, patient preference, and the experience and skills of the clinician. Although non-surgical treatment using gonadotropin-releasing hormone (GnRH) agonist is effective for reducing the size and symptoms of uterine fibroids, surgical treatment is also needed for patients with potential indications such as abnormal uterine bleeding unresponsive to hormone, urinary symptoms or signs such as hydronephrosis and infertility with uterine fibroids as the only abnormal finding.

Among surgical treatments, hysterectomy is a definite method for the treatment of symptomatic uterine fibroids. Especially, laparoscopy-assisted vaginal hysterectomy (LAVH) has more advantages including lesser intraoperative bleeding and shorter hospitalization than abdominal hysterectomy [3]. However, LAVH cannot preserve uterus and can show postoperative complications by the change of pelvic structure [4].

Thus, laparoscopic uterine artery ligation (LUAL) has been introduced in 2001 as an alternative technique for treating uterine fibroids, and significant reduction in the dominant fibroid size (average, 76%) and the uterine volume (average, 46%) were sonographically demonstrated [5]. Thereafter, some studies have reported that LUAL may be effective in relieving the symptoms caused by uterine fibroids, and this procedure can be used in place of hysterectomy [6,7]. Although of these results, there is no study for the comparison of postoperative quality of life (QOL) between LUAL and LAVH.

The current study has been designed to compare the postoperative QOL between LUAL and LAVH, and to evaluate the efficacy of LUAL which can treat symptomatic uterine fibroids with the preservation of uterus.

### Primary outcome

Postoperative QOL 12 months after surgical treatment are evaluated using the European Organization for Research and Treatment of Cancer Quality of Life Questionnaire for Cancer patients (EORTC QLQ-C30) version 3.0., which has been validated to the simplified Korean version [8]. After the evaluation of postoperative QOL, the results will be compared between LUAL and LAVH.

### Secondary outcomes

#### Volume reduction of uterus, uterine fibroids and ovaries by USG

The volume reduction of uterus, uterine fibroids and both ovaries is evaluated in patients treated with LUAL, whereas the volume reduction of only both ovaries is examined in those treated with LAVH.

Improvement of subjective symptoms11-point symptom score, ranging from -5 (markedly worse) to +5 (markedly better), is a method for evaluating either improvement or aggravation of symptoms which patients have, for example, menorrhagia, pain, gastrointestinal discomfort, etc [9]. It is applied in all patients for evaluating the improvement of subjective symptoms by surgical treatment.

#### Evaluation of postoperative vaginal bleeding

In patients treated with LUAL, postoperative vaginal bleeding is measured using a simple visual assessment technique [10]. It is measured monthly by use of the recording sheet including simple visual assessment technique by herself.

#### Postoperative clinical outcomes

Compared with preoperative status, postoperative clinical outcomes are compared between LUAL and LAVH as follows: anemia, hormonal status and serum CA-125 levels; operation time, hospitalization and recovery time to routine life; postoperative pain; conversion to laparotomy; satisfaction of postoperative sexual intercourse; complications associated with surgery.

### Eligibility

#### Inclusion criteria

• Age ≥ 40 years

• Premenopausal patients

• Patients who do not want conception any more

• Patients who agree to the current study protocol with informed consent

• Patients with more than 2 cm sized uterine fibroids on ultrasonography (USG)

• Patients with symptomatic uterine fibroids such as menorrhagia, dysmenorrhea, lower abdominal discomfort or pain, lower back pain and urological symptoms including dysuria and frequency

• Patients without underlying disease affecting QOL

• At least six months interval after last medication if patients have been treated with GnRH agonists.

#### Exclusion criteria

• Age < 40 years

• Patients with subserosal pedunculated uterine fibroids

• Pregnant patients

• Patients with pelvic inflammatory disease (PID) developed within one month

• Patients with suspicious adenomyosis by USG

• Patients contraindicated by surgical treatment

• Patients with previous history of myomectomy, hysterectomy, myolysis, uterine artery embolization

• Patients with underlying disease affecting QOL

• Less than six month's interval after last medication, if patients have been treated with GnRH agonist

### Interventions

#### Laparoscopic uterine artery ligation

After peril-umbilical tracer puncture and the infusion of CO_2 _gas, 2 or 3 tracer punctures are made additionally. Entering the peritoneal cavity, bilateral mesosalpinges including ovarian vessels are coagulated and ligated using hemoclips. Thereafter, right broad ligament is incised between right round ligament and fallopian tube, and the retroperitoneal space is exfoliated using non-traumatic forceps. After right internal iliac artery is seen, the branch of the artery, right uterine artery, is identified. Bipolar coagulation followed by the ligation using hemoclips is applied to right uterine artery. Left uterine artery is ligated according to the procedure for right uterine artery ligation.

#### Laparoscopy-assisted vaginal hysterectomy

After peri-umbilical trocar puncture and the infusion of CO_2 _gas, 2 or 3 trocar punctures are made additionally. Entering the peritoneal cavity, bilateral round ligaments, ovarian ligaments and fallopian tubes are ligated. The uterus is pulled down into the operative field by traction on the each lateral side of the cervical lip. The initial transverse incision through the anterior vaginal wall is made at the cervicovaginal junction and extended laterally on both sides to form encircling incision. The bladder is dissected off the cervix and lower uterine segment anteriorly, and bilateral bladder pillars are ligated. The exfoliation of bladder is advanced to the point where the vesicouterine (U-V) fold is seen, and the U-V fold is incised transversely and the peritoneal cavity is opened. The posterior vaginal wall is dissected off the cervix to the peritoneal reflection of the cul-de-sac. Bilateral cardinal ligaments, uterine vessels and uterosacral ligaments are ligated, and thereby the uterus is delivered through the anterior fornix using tenaculum.

## Outcome measurements

### Primary outcome

After patients are enrolled and randomized, we interview them using EORTC QLQ-C30 before surgical intervention for the evaluation of preoperative QOL. Since the validity of the EORTC QLQ-C30 has already been demonstrated in Republic of Korea [8], and the authors responsible for the validation recommended its usefulness in the current study, we decided to apply it for the evaluation of postoperative QOL in patients with symptomatic uterine fibroids.

The EORTC QLQ-C30 is a 30-item core-cancer-specific questionnaire-integrating system for assessing the health-related QOL in patients participating in international clinical trials [11]. The questionnaire incorporates five functional scales (physical, role, cognitive, emotional, and social), three symptom scales (fatigue, pain, and nausea and vomiting), a global health and QOL scale, and single items for the assessment of additional symptoms commonly reported by cancer patients (e.g., dyspnea, appetite loss, sleep disturbance, constipation, and diarrhea), as well as the perceived financial impact of the disease and treatment [12]. All items are scored on 4-point Likert scales, ranging from 1 ('not at all') to 4 ('very much'), with the exception of two items in the global health/QOL scale which use modified 7-point linear analog scales [11]. After 12 months, all enrolled patients will be interviewed, and the results of EORTC QLQ-C30 will be compared with preoperative results of it (Fig. 1).

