### Secondary outcomes

#### Volume reduction of uterus, uterine fibroids and bilateral ovaries by USG

The method for evaluating volumes of uterus, uterine fibroids and ovaries is as follows: Volume (cm^3^) = maximal sagittal diameter (length, cm) × maximal coronal diameter (width, cm) × maximal antero-posterior diameter (depth, cm) × 0.5233 [13]. Volumes of uterus and uterine fibroids are evaluated in patients treated with LUAL preoperatively and every 3 months, whereas volumes of bilateral ovaries are examined in all patients preoperatively and every 6 months (Fig. 2).

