#### Improvement of subjective symptoms

11-point symptom score are evaluated in all patients 12 months after surgery. Symptoms by uterine fibroids are divided as follows; vaginal bleeding: pelvic pain: urologic symptom; gastrointestinal symptom; other symptoms (Fig. 3). After the completion of the current study, the results are compared between LUAL and LAVH.

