#### Postoperative clinical outcomes

1) Anemia, hormonal status and serum CA-125 levels

Serum hemoglobin levels are evaluated in acute and chronic phases. In the acute phase, we check serum hemoglobin levels preoperatively and 2 days after surgery for comparing the effect of intraoperative blood loss between LUAL and LAVH. In the chronic phase, we check serum hemoglobin levels every 6 months, and we will compare serum hemoglobin levels between the 2 treatment methods.

The evaluation of hormone status is important because Liu et al [5] have reported that 3.5% of patients presented with elevated FSH, suggesting that LUAL can affect preoperative hormonal status. Moreover, serum CA-125 levels are increased in uterine fibroids, whereas they are decreased after the treatment of uterine fibroids. It means that serum CA-125 levels may be one of indirect markers reflecting the change of uterine fibroids [14]. Thus, serum LH, FSH, E2 and CA-125 levels are checked preoperatively and every 6 months, and we will compare these values between the 2 treatment methods.

2) Operation time, hospitalization and recovery time to routine life

The operation time is recorded in all patients for the investigation of whether there is a significant difference in the time between LAUL and LAVH. All patients are discharged as soon as possible if they are considered not to be hospitalized, and we will evaluate hospitalization and recovery time to routine life in all patients because the 2 parameters may reflect the time from surgery to healthy status.

3) Postoperative pain

Pain intensity is measured with a visual analogue scale (VAS), a 100-mm horizontal line with anchors of no pain and worst possible pain. The VAS is scored by measuring in millimeters the distance from the side marked no pain to the edge of the mark made by the patient. Possible scores ranges from a minimum of 0 to a maximum of 100 mm. The VAS scale is presented to the patients individually by instructed nurses who are unaware of assignments. After the VAS scales are evaluated during postoperative 3 days, the sums of scores will be compared between LUAL and LAVH.

4) Conversion to laparotomy

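### Quality of life is measured once after surgery, at 12 months, so dropout that follows the postoperative course cannot be adjusted for with any postoperative QOL data; a 6-month QLQ-C30 would help cheaply

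*Protocol article*

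**What the plan says.** The article fixes the primary outcome at one time: "Postoperative QOL 12 months after surgical treatment are evaluated using the European Organization for Research and Treatment of Cancer Quality of Life Questionnaire". The section on outcome measurements adds the baseline, "we interview them using EORTC QLQ-C30 before surgical intervention for the evaluation of preoperative QOL", and a single later interview, "After 12 months, all enrolled patients will be interviewed, and the results of EORTC QLQ-C30 will be compared with preoperative results of it".

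Other measurements are more frequent:
- In both arms, "volumes of bilateral ovaries are examined in all patients preoperatively and every 6 months".
- Under postoperative clinical outcomes, "serum LH, FSH, E2 and CA-125 levels are checked preoperatively and every 6 months", and "In the chronic phase, we check serum hemoglobin levels every 6 months". Both sets are compared between the treatments.
- In the LUAL arm only, "Volumes of uterus and uterine fibroids are evaluated in patients treated with LUAL preoperatively and every 3 months", together with a monthly bleeding record.

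The other patient-reported symptom measure also comes late: "11-point symptom score are evaluated in all patients 12 months after surgery". No 6-month patient-reported measure common to both arms is stated.

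The statistical analysis section promises an intention-to-treat analysis of everyone randomised, then removes patients whose QLQ-C30 outcome is missing. The analysis is an ANCOVA with baseline adjustment, although a later sentence makes that adjustment depend on a test of baseline imbalance.

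**The concern.** Each woman has at most one postoperative QOL value. If she attends at 6 months and is then lost, her QOL after surgery is unknown and she leaves the primary comparison.

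This matters if the reason for leaving is how she feels after the operation. The women know whether they kept the uterus, and those whose symptoms persist after LUAL may be the likeliest to leave. The contact schedules also differ: LUAL has 3-monthly scans and monthly charts, whereas the regular contact stated for LAVH is 6-monthly. Retention could therefore differ by arm.

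If women doing badly after LUAL are lost, the remaining cases flatter LUAL. The article's Discussion hopes to show similar efficacy and bases the next study on finding no difference, so this error could hide a true deficit of LUAL.

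**Working it through.** **Inputs from the article.** Total 200, allocation 1:2 (67 LUAL, 133 LAVH), difference 10%, power 90%, level 0.05. The SD, the dropout rate and the correlations between visits are not given.

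**Step 1: scale.** Read 10% as 10 points on a 0–100 scale and solve the two-sided normal formula for the SD:

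SD = 10 / [(1.960 + 1.282) × √(1/67 + 1/133)] = 10 / (3.242 × 0.1498) ≈ 20.6.

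The figure of 200 cannot be reproduced from the stated inputs, because it needs this unstated SD. An SD of 20 is therefore a reasonable working value, but it is an assumption.

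**Step 2: model for dropout (all assumed).** No true difference; SD 20; correlation 0.4 between baseline and either later score, and 0.65 between 6 and 12 months. Dropout follows

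logit P(drop) = logit(p₀) − k × LUAL × (Q − mean)/SD,

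with p₀ = 0.10 or 0.20 and k = 1 or 1.5. Q is the 6-month or the 12-month score, and LUAL is 1 in that arm and 0 otherwise. Compare the complete-case ANCOVA on baseline with an analysis that also uses the 6-month score.

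**Step 3: results.** Bias in points, positive in favour of LUAL.

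| Dropout in LUAL | Baseline only | With 6-month score | Removed |
|---|---|---|---|
| Follows 6-month QOL, all seen at month 6 | 1.1 to 2.9 | about 0 (at most 0.15) | nearly all |
| Same, half leave before month 6 | about 1.25 to 3.0 | 0.6 to 1.3 | about half |
| Follows 12-month QOL, all seen at month 6 | 2.1 to 5.1 | 1.45 to 3.7 | about 30% |
| Follows 12-month QOL, half leave before month 6 | 2.1 to 5.1 | – | about 15% |
| Unrelated to QOL, 20% lost | 0 | 0 | – |

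In the third row, 1 − 1.45/2.1 = 0.31 and 1 − 3.7/5.1 = 0.27.

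**Step 4: error rate.** In the first row, bias over SD of the estimate runs from 1.13/2.88 = 0.39 to 2.92/3.10 = 0.94. The two-sided 5% error becomes Φ(−1.96 + r) + Φ(−1.96 − r), which is 6.8% at r = 0.39 and 15.6% at r = 0.94.

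**Step 5: precision.** With 20% uninformative loss, the SD of the estimate falls from 3.08 to 2.97. Variance falls by 1 − (2.97/3.08)² = 7%.

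**Step 6: other assumptions.** Take SD 20.57, dropout 25% in LUAL and 10% in LAVH, slopes 0.5 to 1, correlations 0.3–0.5 (baseline with later scores) and 0.5–0.7 (6 with 12 months).
- Dropout follows 6-month QOL: complete-case bias is 1.0 to 2.0, imputation from baseline QOL leaves it at 1.0 to 2.0, and adding a 6-month score brings it to between −0.1 and 0.1.
- Dropout follows 12-month QOL: 1.9 to 4.0 falls only to 1.2 to 3.3, a reduction of about 20–35%.

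Both sets agree. Baseline QOL alone does not help when the postoperative course drives dropout. A 6-month score always helps, but by very different amounts.

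**The case against.** A single prespecified endpoint at 12 months is a legitimate choice. It matches the one-year participation and is used consistently for QOL, symptoms, sexual satisfaction and the power calculation. That stands: nothing here contradicts itself.

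A reader might infer that dropout differing by arm cannot be corrected at all. The article does not support this. Unequal dropout rates alone do not bias a baseline-adjusted ANCOVA, and dropout depending only on arm and baseline QOL is handled if baseline is always in the model. Women lost after month 6 also leave haemoglobin, hormone, CA-125 and ovarian data, and in LUAL bleeding charts and uterine and fibroid volumes. These can serve as auxiliary variables. They are probably weak predictors of QOL, and the charts and uterine volumes exist in one arm only, but they are not nothing.

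A reader might also infer that a 6-month questionnaire would bring the bias to zero. That happens only when 6-month QOL is the sole driver of dropout and every dropout has been seen at month 6, which the first row of the table builds in.

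Two further limits stand. Every magnitude is assumed. And recruitment closed in June 2008, so many women may already be past month 6.

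A fuller protocol or an analysis plan may hold more detail on the model, but the article states the timing of each outcome, and no analysis plan can supply QOL that was not collected.

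**Conclusion.** The point holds as a low-severity design improvement. With one postoperative QLQ-C30 and exclusion of women who lack it, dropout related to the postoperative QOL course cannot be adjusted for with any postoperative QOL data.

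Under the stated assumptions, the bias towards LUAL is about 1–3 points if dropout follows 6-month QOL and about 2–5 points if it follows 12-month QOL, against a planned difference of 10 points on the reading in step 1. If dropout is unrelated to QOL there is no bias, and the gain is only about 7% in variance at 20% loss.

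The real dropout rate and its cause are unknown, so confidence in the size is low. The weakness is the single measurement combined with the exclusion rule, not the choice of 12 months.

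**What to change.** - Give the QLQ-C30 with the existing 6-month assessment in both arms, now only for women not yet past it. Use the same timing in both arms.
- Keep the 12-month between-arm contrast as the primary test.
- Replace the complete-case exclusion with a repeated-measures model (baseline, arm, visit, arm by visit) that keeps women who have a 6-month but no 12-month value. Include baseline QOL whatever an imbalance test shows.
- Report the 6-month contrast as secondary.
- State that women lost before month 6, and dropout driven by QOL after month 6, remain only partly addressed.

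The cost is a 30-item questionnaire, a few minutes of patient and staff time per woman, and a short amendment. Assessments are already scheduled every 6 months, so no extra visit should be needed. For women already past month 6 the value cannot be recovered, so the benefit shrinks the later the change is made.

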**Figure 1 F1:**
[figure not shown]
**European Organization for Research and Treatment of Cancer Quality of Life Questionnaire for Cancer patients (EORTC QLQ-C30) version 3.0. for comparing postoperative quality of life between laparoscopic uterine artery ligation and laparoscopy-assisted vaginal hysterectomy**.

### Secondary outcomes

#### Volume reduction of uterus, uterine fibroids and bilateral ovaries by USG

The method for evaluating volumes of uterus, uterine fibroids and ovaries is as follows: Volume (cm^3^) = maximal sagittal diameter (length, cm) × maximal coronal diameter (width, cm) × maximal antero-posterior diameter (depth, cm) × 0.5233 [13]. Volumes of uterus and uterine fibroids are evaluated in patients treated with LUAL preoperatively and every 3 months, whereas volumes of bilateral ovaries are examined in all patients preoperatively and every 6 months (Fig. 2).

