Although the 2 surgical treatments are similar in terms of laparoscopic managements, LUAL can preserve uterus with exploration of retroperitoneal space and ligation of uterine artery. On the other hand, LAVH removes uterus without the exploration of retroperitoneal space. Thus, these differences can contribute the rate of conversion from laparoscopic approach to laparotomy. We will compare the rate of conversion to laparotomy between LUAL and LAVH.

6) Satisfaction of postoperative sexual intercourse

Since patients treated with LUAL have cervices while those treated with LAVH have no cervices postoperatively, types of surgical treatment can affect postoperative sexual intercourse. Thus, the change of satisfaction of sexual intercourse will be evaluated after 12 months after surgery. The satisfaction of sexual intercourse is scored on 3-point scales, consisting of -1 ('not satisfied'), 0 ('no change') and +1 ('satisfied').

7) Complications associated with surgery

We divided complications associated with surgery as follows: intraoperative complication; complication during hospitalization; complication within 1 month; complication within 12 months. Moreover, the severity of the complications is defined as follows [9].

(1) Grade 1: no consequence for the patients and necessitated no or only nominal treatment (e.g. arterial spasm, postpuncture hematoma, surgical wound hematoma, vaginal discharge, urinary retension, thigh paresthesia).

(2) Grade 2: necessitated non-life-threatening additional treatment and had no sequelae of patients (e.g. urinary infection, severe pelvic pain, renoureteral colic, vulvovaginitis, anal fissure).

(3) Grade 3: death or complication that represents a threat to the patient's life or a source of permanent sequelae (e.g. death, deep vein thrombosis, transfusion, intraabdominal abscess, vesical fissure, surgical wound abscess).

After the completion of the current study, we will compare these results between the 2 treatment methods.

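### Preoperative uterine and fibroid volume is specified for LUAL women only, although every woman is scanned before surgery, so it cannot describe the arms or sharpen the operative comparisons

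*Protocol article*

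**What the plan says.** Under *Outcome measurements, Secondary outcomes*, the Protocol article sets the volume schedule by arm. For the uterus and fibroids: "Volumes of uterus and uterine fibroids are evaluated in patients treated with LUAL preoperatively and every 3 months". For the ovaries: "volumes of bilateral ovaries are examined in all patients preoperatively and every 6 months". The earlier list of secondary outcomes makes the same split: "the volume reduction of only both ovaries is examined in those treated with LAVH".

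The inclusion criteria require a fibroid larger than 2 cm on ultrasonography. Every woman has therefore been scanned before her arm is known, and she is scanned again before surgery for ovarian volume.

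Under *Postoperative clinical outcomes*, several measures of the operation itself are compared between the arms. On operation time: "The operation time is recorded in all patients for the investigation of whether there is a significant difference in the time". Haemoglobin is taken before surgery and "2 days after surgery for comparing the effect of intraoperative blood loss between LUAL and LAVH". On conversion: "We will compare the rate of conversion to laparotomy between LUAL and LAVH".

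The *Statistical analysis* section assigns all comparisons other than the primary one to the t-test, the Mann-Whitney test and the chi-square test, without covariates. The only baseline imbalance check and covariate it describes concern the EORTC score. Randomisation is central, concealed and blocked, and no stratification by uterine or fibroid size is described.

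**The concern.** Restricting follow-up uterine volumes to LUAL is unavoidable. Restricting the preoperative value is not, because before surgery both arms can be measured in the same way. The article names the preoperative measurement and gives it to one arm, so this is a stated rule and not a detail left out by condensation.

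Uterine size is a plausible baseline determinant of how long an operation takes and how much blood is lost. That is a clinical premise; the documents do not quantify it. If it holds, two things are lost. The report cannot show from the planned volume data whether the arms had similar disease at entry. And a later decision to adjust the operative comparisons for volume could not be carried out, because about two thirds of the women would have no value.

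**Working it through.** **Inputs.**
- Total of 200 women (*Statistical analysis*), allocated 1:2 LUAL to LAVH (*Study design*): 200/3 ≈ 67 LUAL and 133 LAVH.
- Share of variance in operation time explained by preoperative uterine volume, R²: not in the documents; assumed 10–30%.

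**The plan's own figure.** The 200 women are for 90% power on quality of life. No SD is given, so the figure cannot be reproduced. If the 10% difference is read as 10 points with a two-sided 5% test, the implied SD at 67:133 is 10 / [(1.960 + 1.282) × 0.150] = 20.6. Nothing below depends on this. No power is stated for operation time.

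**Step 1: the passages side by side.**

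| Item | LUAL | LAVH |
|---|---|---|
| Eligibility ultrasound | yes | yes |
| Preoperative scan for ovarian volume | yes | yes |
| Preoperative uterine and fibroid volume | yes | not planned |
| Operation time, haemoglobin change, conversion compared | yes | yes |

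The scan exists in both arms; the reading is planned in one.

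**Step 2: what adjustment would be worth.** With a linear covariate explaining R² of the outcome variance within arms, residual variance falls to (1 − R²). The equivalent unadjusted sample is 200 / (1 − R²), and the confidence interval width is multiplied by √(1 − R²).

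| Assumed R² | Equivalent sample | Gain | Width factor |
|---|---|---|---|
| 0.10 | 200/0.90 = 222 | 11% | 0.95 |
| 0.20 | 200/0.80 = 250 | 25% | 0.89 |
| 0.30 | 200/0.70 = 286 | 43% | 0.84 |

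**Step 3: how large a chance difference in volume could be.** The standard error of a standardised baseline difference is √(1/67 + 1/133) = 0.150. Its 95% chance range is 1.96 × 0.150 = ±0.29 SD. The probability of exceeding 0.2 SD in either direction is 2[1 − Φ(0.2/0.150)] = 18%; for 0.3 SD it is about 4.5%.

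An imbalance of 0.2 SD would shift the unadjusted comparison by r × 0.2, where r = √R². With r from √0.10 = 0.32 to √0.30 = 0.55, that is 0.06 to 0.11 SD of operation time. The standard error of the unadjusted test already allows for variation of this kind.

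**The case against.** The strongest case against is that the passage schedules an outcome, volume reduction, which has no meaning once the uterus is removed. It is not a list of baseline data, and a condensed article may leave the baseline table to the full protocol. This stands in part. The eligibility ultrasound gives some size information in both arms, so a reader who inferred that imbalance in disease size is wholly invisible would go too far. But a 2 cm threshold is not a volume, and the article expressly allocates the preoperative volume by arm.

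A reader might also infer that the operative comparisons are biased or that their error rate is inflated. The documents do not support that. Allocation is concealed and central, so the unadjusted tests are valid over repeated randomisation, and chance imbalance is part of their 5%. A larger error rate appears only if one conditions on an unlucky allocation.

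Nor do the missing volumes cause the lack of adjustment. The *Statistical analysis* section chooses unadjusted tests for all other comparisons in any case, and further covariates could properly be left to an analysis plan that is not shown.

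Two smaller points also stand. LUAL leaves the uterus in place and LAVH delivers it through the vagina, so size may affect the two operations differently; the gains in Step 2 assume a similar slope in both arms. And recruitment closed in June 2008, so for women already operated on the values depend on stored images or reports, which the article does not mention. A scan taken for the ovaries need not contain the uterine diameters.

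**Conclusion.** The point holds as a cheap improvement to secondary outcomes. The plan measures a useful baseline variable in one arm only, although women in both arms are scanned before surgery. The planned volume data therefore cannot describe disease size by arm or be used to gain precision.

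On the assumption that volume explains 10–30% of the variance in operation time, the forgone gain for that outcome is equivalent to about 11–43% more women, or a confidence interval 5–16% narrower. If the true share is smaller, so is the gain. A chance difference in volume above 0.2 SD would arise in about 18% of trials of this size and ratio, which is reason enough to tabulate it.

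No error in the planned tests is shown. Blood loss is not compared directly; its effect is inferred from haemoglobin. The primary quality-of-life comparison is unaffected.

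**What to change.** - Record preoperative uterine and dominant-fibroid volume in all randomised women, using the formula in the same section, from the scans already done. For women already operated on, use existing images or reports where available, and state how many values are missing in each arm.
- Report both volumes by arm in the baseline table.
- Before the operative results are examined, prespecify log preoperative uterine volume as a covariate for operation time and for day-2 haemoglobin change, the latter also adjusted for preoperative haemoglobin. A sensitivity analysis allowing the slope to differ by arm would address the different nature of the two operations.
- Keep follow-up uterine and fibroid volumes in LUAL women only.

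The formula needs three diameters per structure, so the uterus and one fibroid take six per LAVH woman. There is no extra visit or procedure. The drawback is some reading time and possibly incomplete values in the LAVH arm.
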